### Statistical Analysis

Baseline characteristics will be reported by group assignment in the form of means (standard deviations) and medians (interquartile ranges) for continuous variables, as appropriate, and proportions for categorical variables. The analysis will use two-sample *t*-tests to compare continuous variables and χ^2^-tests to compare categorical variables between the pharmacist-directed intervention and usual care groups. All participants will be included according to the intention-to-treat principle for all endpoints. A per protocol analysis will be reported as a secondary analysis to evaluate whether study dropout significantly influenced the outcome of the trial. Because the total study population is 100, subgroup analyses are not planned for this study due to insufficient power. Since this is a pilot and feasibility study, no formal power analysis has been performed to inform the sample size. However, given *N* = 50 in each study arm and under the assumption of similar BNP changes as in STOP-HF (7), the study would have 80% power to detect a 12 pg/mL mean difference in the change in BNP between the two study arms.

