### Heart Failure Risk Assessment

The 2017 focused update of the American College of Cardiology/American Heart Association (ACC/AHA) Guideline for the Management of HF highlights the potential role of natriuretic peptide biomarker screening, followed by team-based care, in those at risk for HF (6). This guideline recommendation was informed by two randomized controlled trials, the STOP-HF trial and the PONTIAC trial, which demonstrated that referral to collaborative cardiology care based on natriuretic peptide value cutoffs in patients at high cardiovascular risk may prevent HF (7, 8). However, in STOP-HF, only 27% of patients had a BNP > 50 pg/mL, the threshold for referral to cardiology. In addition, a risk factor-based approach that treats all risk factors equally (as in STOP-HF) or requires the presence of a particular risk factor such as diabetes (as in PONTIAC) may miss some patients at high risk due to elevations below treatment thresholds in multiple risk factors and may over-sample some patients at low risk, such as younger adults with a single risk factor. In contrast, multivariable risk prediction equations for HF, such as the Pooled Cohort equations to Prevent HF (PCP-HF) (9), that incorporate clinical measures readily available in primary care settings may improve identification of those at risk for HF who may merit more intensive prevention strategies.

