### Study Protocol

A research coordinator will call patients listed in the recruitment report to confirm eligibility, describe the study, and ask if they are interested in participating. If so, the research coordinator will review study procedures over the phone and schedule a visit in the research clinic. Participants will be emailed a link to sign electronic consent (e-Consent) and complete a baseline health and lifestyle questionnaire. The e-Consent option will offer flexibility and minimize in-person time to decrease participant burden during and after the COVID-19 pandemic. The questionnaire is composed of previously validated questions from the World Health Organization, Multi-Ethnic Study of Atherosclerosis (MESA), and EuroQol. Participants who are unwilling or unable to complete these procedures online will be instructed to arrive 30 min before their scheduled visit in order to sign written consent and complete the questionnaire in person. After consent is obtained, participants will then be randomized in 1:1 fashion to intervention vs. usual care (Figure 1). The randomization table will be generated using random permuted blocks of sizes four and six by a statistician with no other involvement in the study.

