### Outcomes

The primary outcome is change in BNP at 1 year. Secondary outcomes include change in hs-cTn, systolic and diastolic blood pressure, weight and body mass index, serum glucose and low density lipoprotein cholesterol, estimated glomerular filtration rate and creatinine, and current smoking at 1 year. Exploratory outcomes include medication adherence and changes in echocardiographic parameters such as left ventricular mass index, diet and physical activity, and health utility at 1 year. Adherence to medications is measured using the same questionnaire as the Atherosclerosis Risk in Communities (ARIC) study: the four-item Morisky Green Levine Scale, frequency of non-adherence in the past 4 weeks, and direct measure of adherence in the past 4 weeks (28). Feasibility will also be examined by monitoring participant retention rates. Retention will be defined as completion of the 1-year study protocol and measured as the proportion of enrolled participants in each arm who successfully complete the study. All demographics (e.g., sex, race, ethnicity, education), health behaviors (e.g., smoking, diet, physical activity), and patient-centered outcomes (e.g., health-related quality of life) are self-reported.

The following serious adverse events will be reported: echocardiogram or troponin alert (at baseline or 1-year follow-up), death, hospitalization, or ER visit (all at 1-year follow-up, or sooner if the study team becomes aware of the adverse event). All adverse events will be determined by chart review and personally adjudicated by the principal investigator. As a process of care intervention using guideline-directed medical therapy (rather than a trial of a novel therapy), drug-related adverse events will not be reported for this study.

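### The stated t-test on raw BNP change is valid but less efficient than ANCOVA on the baseline BNP already measured in every participant

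*Protocol article*

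**What the plan says.** The Outcomes section of the protocol article states: "The primary outcome is change in BNP at 1 year". The Statistical Analysis section then says "The analysis will use two-sample *t*-tests to compare continuous variables" between the two arms. It names no covariate, no transformation and no other test for continuous data. Medians with interquartile ranges are allowed where suitable, but only for describing baseline characteristics.

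The scale of the primary comparison follows from the power sentence, which claims "80% power to detect a 12 pg/mL mean difference in the change in BNP between the two study arms", "given *N* = 50 in each study arm" and "under the assumption of similar BNP changes as in STOP-HF". The section also says that this is a pilot and that no formal power analysis set the sample size.

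Under Study Protocol, every participant has blood drawn at baseline for BNP and hs-cTn. Randomization is 1:1 in permuted blocks of four and six, and no stratification factor is mentioned.

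**The concern.** A change score uses baseline in one fixed way: it subtracts all of it. ANCOVA estimates how much of the baseline value carries over to follow-up and removes only that much. Unless the true slope is 1, the change score is noisier. In an arm that starts higher by chance, it also counts some regression to the mean as treatment effect. With about 50 per arm, chance differences in baseline BNP are to be expected.

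A second question is the scale. BNP is a positive marker, and such markers are often right-skewed. If that holds here, a few participants with high values contribute much of the variance of absolute change, and a log scale would be more efficient. The same applies to hs-cTn.

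What is at stake is precision. The Discussion uses change in BNP as the pilot's measure of limited efficacy, and the rationale section says the pilot should supply preliminary data for designing a larger trial. A wider interval than necessary weakens both uses.

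**Working it through.** **Inputs from the protocol article.** n = 50 per arm, 1:1 allocation, difference 12 pg/mL, power 80% (Statistical Analysis; Study Protocol). In STOP-HF, 27% of patients had BNP above 50 pg/mL (Heart Failure Risk Assessment).

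**Inputs assumed, because the article does not give them.** Two-sided alpha 0.05; baseline-to-1-year correlation r of 0.5 to 0.8; equal SDs at the two visits; and, in step 3 only, the shape of the BNP distribution and the form of the effect.

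**Step 1: the stated power.** No SD is printed, so the 80% cannot be checked independently. It can only be solved for the SD it implies:

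SD = 12 / [(1.960 + 0.842) × √(2/50)] = 12 / (2.802 × 0.2) = 21.4 pg/mL.

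The noncentral t version gives 21.2.

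**Step 2: baseline adjustment on the raw scale.** With equal SDs at both visits, the variance of the ANCOVA estimate relative to the change-score estimate is (1 + r)/2. The detectable difference is 12 × √[(1 + r)/2]. Power is Φ(12/SE − 1.960), with SE = 21.4 × √[(1 + r)/2] × 0.2.

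| r | Variance ratio | SE (pg/mL) | Power at 12 pg/mL | Difference detectable at 80% power | n per arm for 80% power |
|---|---|---|---|---|---|
| change score | 1.00 | 4.28 | 80% | 12.0 | 50 |
| 0.8 | 0.90 | 4.06 | 84% | 11.4 | 45 |
| 0.7 | 0.85 | 3.95 | 86% | 11.1 | 43 |
| 0.6 | 0.80 | 3.83 | 88% | 10.7 | 40 |
| 0.5 | 0.75 | 3.71 | 90% | 10.4 | 38 |

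Adjustment alone is worth 4 to 10 points of power, or 5 to 12 participants per arm.

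**Step 3: log scale, under an assumed shape.** Simulated trials had 50 per arm and log-normal BNP. The median was set so that 27% of baseline values exceed 50 pg/mL. The intervention lowered BNP by 30%, a mean difference of about 12.4 to 12.5 pg/mL in the first two rows. Each row is 10,000 trials.

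| Log-SD | r | Control-arm change SD (pg/mL) | Raw-change t-test | Raw ANCOVA | Log ANCOVA |
|---|---|---|---|---|---|
| 0.6 | 0.7 | 22 | 83% | 95% | 98% |
| 0.7 | 0.8 | 23 | 81% | 93% | 99% |
| 0.9 | 0.7 | 43 | 40% | 57% | 79% |
| 1.1 | 0.7 | 68 | 24% | 34% | 61% |

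Only the first two rows have a change SD close to the 21.4 pg/mL of step 1, and there the t-test has about the power the article claims. The last two rows need two to three times that SD, so they do not describe the trial as the article presents it.

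**Step 4: validity.** In simulations with no treatment effect, log-SD 0.3 to 1.0 and r 0.5 to 0.85, the raw-change t-test rejected in 3.9% to 5.6% of trials. Its type I error is close to nominal.

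**The case against.** The strongest reply is that nothing here is an error. Under randomization the change-score comparison is unbiased, chance imbalance is already reflected in its standard error, and its type I error is near 5%. That stands: the point concerns efficiency only.

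A reader might infer that the test throws the baseline away. It does not, since a change score subtracts it. A reader might also infer that a few high values dominate the result. The article gives no mean, SD or distribution of BNP for this trial. Its only anchor, "in STOP-HF, only 27% of patients had a BNP > 50 pg/mL", is one quantile from another population, and a symmetric distribution could have it too. Nor do the documents support saying that much of the power is lost. That needs marked skew with a change SD far above the one the article's own power figure implies.

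The log-scale simulations also favour log ANCOVA by construction, because they generate the data that model assumes. They show what could be gained, not what will be.

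On scope, the t-test sentence follows the one on baseline characteristics, and an analysis plan that is not shown could add adjustment. But the t-test is the only test named, the power sentence matches it, and intention to treat for all endpoints is stated immediately afterwards. This is a stated choice rather than a missing detail.

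Finally, the study is a pilot, and the later trial is meant to evaluate clinical events, so the SD of BNP change may not set its size. That lowers the stakes. It does not remove the pilot's stated purpose of judging limited efficacy from BNP.

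**Conclusion.** The point holds as a matter of efficiency. The stated primary test is valid but less precise than an analysis that uses the same data with baseline as a covariate. At the implied change SD of 21.4 pg/mL, raw-scale ANCOVA would raise power for 12 pg/mL from 80% to about 84-90%. This rests on two-sided 0.05, equal SDs at both visits and a correlation between 0.8 and 0.5. A higher correlation would shrink the gain (82% at r = 0.9).

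The further gain from a log scale, from about 81-84% with the raw-change t-test to about 98% with log ANCOVA, is conditional on a log-normal shape and a proportional effect. The documents establish neither, so it supports preferring the log scale but does not measure a loss in this trial.

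**What to change.** In the Statistical Analysis section, make the primary analysis an ANCOVA of 1-year BNP with arm and baseline BNP as covariates. Preferably log-transform both BNP values and report the adjusted geometric mean ratio with its 95% CI. Treat hs-cTn the same way, and use baseline-adjusted ANCOVA for the other continuous secondary outcomes (blood pressure, weight and body mass index, glucose, LDL cholesterol, eGFR and creatinine). Keep the raw-change t-test as a supportive analysis, so that the 12 pg/mL power statement can still be interpreted.

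This needs no new data, visits or participants. The cost is that a log-scale primary result is a ratio rather than a difference in pg/mL, so the effect measure changes and the existing power sentence then describes the supportive analysis. If the pg/mL scale matters most to the investigators, raw-scale ANCOVA keeps it and still gives the gain in step 2 of the working. Either choice should be fixed before outcome data are seen.

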## Abstract

**Background:** Given rising morbidity, mortality, and costs due to heart failure (HF), new approaches for prevention are needed. A quantitative risk-based strategy, in line with established guidelines for atherosclerotic cardiovascular disease prevention, may efficiently select patients most likely to benefit from intensification of preventive care, but a risk-based strategy has not yet been applied to HF prevention.

**Methods and Results:** The Feasibility of the Implementation of Tools for Heart Failure Risk Prediction (FIT-HF) pilot study will enroll 100 participants free of cardiovascular disease who receive primary care at a single integrated health system and have a 10-year predicted risk of HF of ≥5% based on the previously validated Pooled Cohort equations to Prevent Heart Failure. All participants will complete a health and lifestyle questionnaire and undergo cardiac biomarker (B-type natriuretic peptide [BNP] and high-sensitivity cardiac troponin I [hs-cTn]) and echocardiography screening at baseline and 1-year follow-up. Participants will be randomized 1:1 to either a pharmacist-led intervention or usual care for 1 year. Participants in the intervention arm will undergo consultation with a pharmacist operating under a collaborative practice agreement with a supervising cardiologist. The pharmacist will perform lifestyle counseling and recommend initiation or intensification of therapies to optimize risk factor (hypertension, diabetes, and cholesterol) management according to the most recent clinical practice guidelines. The primary outcome is change in BNP at 1-year, and secondary and exploratory outcomes include changes in hs-cTn, risk factor levels, and cardiac mechanics at follow-up. Feasibility will be examined by monitoring retention rates.

**Conclusions:** The FIT-HF pilot study will offer insight into the feasibility of a strategy of quantitative risk-based enrollment into a pharmacist-led prevention program to reduce heart failure risk.

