**Figure 1 F1:**
[figure not shown]
Overview of the FIT-HF study. Participants will be recruited by invitation from the eligible study population using an electronic health record-based report. They will complete eConsent and questionnaires online and have biomarkers measured and echocardiograms performed at baseline and 1 year. In the interim, they will be randomized 1:1 to a pharmacist-led intervention or to usual care. HF represents heart failure; EDW Enterprise Data Warehouse. Created with BioRender.com.

All participants will undergo phlebotomy for measurement of BNP, hs-cTn, basic metabolic panel, lipid panel, and biorepository storage, and baseline echocardiography with Doppler measurements. All participants will also undergo measurement of vital signs and receive an educational packet of information from the Centers for Disease Control and Prevention and American Heart Association on signs and symptoms of HF and heart-healthy lifestyle.

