Participants who are randomized to the intervention arm will receive a referral to the pharmacist-led intervention (supervised by an attending cardiologist), and have their first visit on the same day as the baseline testing. Two pharmacy residents will deliver the intervention under the supervision of an attending pharmacist. Residents have received standardized training on lifestyle modification and risk factor management through the residency program. Pharmacists will review participants' medications and may make adjustments according to a medication protocol (Figure 2) for blood pressure, glucose, and lipid control according to the latest evidence-based practice guidelines. Specifically, the medication protocol specifies blood pressure control according to the protocol employed by Kaiser Permanente Health (24), consideration of SGLT-2 inhibitor initiation in patients with diabetes per ACC/AHA and American Diabetes Association (ADA) guidelines (5, 25), and statin initiation or intensification per the 2018 ACC/AHA cholesterol guideline (20). Pharmacists will additionally counsel patients regarding heart-healthy lifestyles and may order laboratory tests when medications are added to follow potassium levels, kidney function, or other relevant laboratory parameters according to the standard of care. Adherence to follow-up lab tests is monitored by the pharmacists, with reminders sent at their discretion according to their typical clinical practice. The study population comprises patients who receive their usual care on the same medical campus as the study site, mitigating access to care limitations for the purposes of this pilot study. The pharmacist visits are provided at no cost to participants; medications are e-prescribed to participants' preferred pharmacies according to the standard of care and are billed through participants' insurance. The results from participants' BNP, hs-cTn, and echocardiography will be provided to them and their primary care physicians as well as the pharmacist and cardiologist team members. Participants in the intervention arm will receive follow-up from the pharmacist team approximately every 3 months for a period of 1 year. Follow-ups will be clinical telephone visits structured similarly to the baseline visit, with interim review of laboratory values, if applicable, for medication monitoring and titration. The pharmacist team will provide a detailed note in the electronic medical record to the primary care doctor after every clinical encounter.

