
**Figure 2 F2:**
[figure not shown]
Pharmacist-directed intervention treatment algorithm. The treatment algorithm was derived from professional society guidelines for the primary prevention of cardiovascular disease as well as blood pressure, glucose, and lipid lowering. Special consideration is given to the early initiation of SGLT-2 inhibitors in patients with diabetes, given the evidence supporting their efficacy in heart failure prevention and current guideline recommendations. BP represents blood pressure; ACEi angiotensin converting enzyme inhibitor; ARB angiotensin receptor blocker; CCB calcium channel blocker; SMBG self-monitored blood glucose; eGFR estimated glomerular filtration rate; PCP primary care physician; DM diabetes mellitus; SBP systolic blood pressure; DBP diastolic blood pressure; HTN hypertension.

The participants (and their primary care physicians) who are randomized to usual care will be blinded to their 10-year heart failure risk estimates as well as biomarker and echocardiography results, unless there are critical or alert values from the hs-cTn (i.e. >500 pg/mL) or echocardiography (see Supplementary Methods), in which case their primary care physician will be informed. All patients will be requested to repeat the health and lifestyle questionnaire and schedule an in-person visit at 1-year follow-up. At this visit, all participants will undergo repeat measurement of vital signs and anthropometrics, phlebotomy, and echocardiography. The 1-year follow-up time was selected based on a limited duration by which a significant change in risk factor control would be expected based on prior studies (11, 13, 18). Participants receive free parking for all study-related visits and are paid $25 at the end of the study for their time spent participating.

Study data will be collected and managed using REDCap (Research Electronic Data Capture) electronic data capture tools hosted at Northwestern University (26, 27). REDCap is a secure, web-based software platform designed to support data capture for research studies, providing (1) an intuitive interface for validated data capture; (2) audit trails for tracking data manipulation and export procedures; (3) automated export procedures for seamless data downloads to common statistical packages; and (4) procedures for data integration and interoperability with external sources.

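### The per-protocol analysis cannot show whether dropout influenced the BNP result, so using it as the dropout check would be falsely reassuring

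*Protocol article*

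**What the plan says.** Three statements in the protocol article bear on this point.

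- **Outcome and timing.** Under Outcomes: "The primary outcome is change in BNP at 1 year". The Figure 1 legend says that participants "have biomarkers measured and echocardiograms performed at baseline and 1 year", and Study Protocol says of the 1-year visit: "At this visit, all participants will undergo repeat measurement of vital signs and anthropometrics, phlebotomy, and echocardiography". The pharmacist contacts in between are in the intervention arm only and are by telephone: "Follow-ups will be clinical telephone visits structured similarly to the baseline visit". Laboratory review at those contacts is for medication monitoring. No interim BNP is described for either arm.
- **Analysis.** Under Statistical Analysis, continuous variables are compared by two-sample t-test, and "All participants will be included according to the intention-to-treat principle for all endpoints". The next sentence gives the per-protocol analysis its purpose: "A per protocol analysis will be reported as a secondary analysis to evaluate whether study dropout significantly influenced the outcome of the trial".
- **Completion.** Under Outcomes: "Retention will be defined as completion of the 1-year study protocol". It is reported as a proportion in each arm.

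The article does not define the per-protocol set and states no expected dropout rate.

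**The concern.** A comparison of ITT and per-protocol results can reveal the effect of dropout only if at least one of the two analyses holds information on what happened to those who dropped out. Here neither need do so. With two BNP measurements, a person who misses the second has no observed change, and a per-protocol analysis cannot supply one.

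The risk lies in how the result would be read. Two similar estimates would be reported, in line with the plan, as evidence that dropout did not influence the outcome, whatever the missing values were. Unequal dropout is plausible by design. The intervention arm is contacted about every 3 months and receives its results. The usual-care arm is blinded to its results except for alert values, and no comparable interim study contact is described for it. The Discussion treats BNP change as the evidence of limited efficacy and expects the data to shape a later outcomes trial, so an unfounded all-clear would be carried forward.

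**Working it through.** **Inputs from the article.** 50 participants per arm; 80% power for a 12 pg/mL difference in BNP change; BNP at baseline and 1 year; two-sample t-test.

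**The plan's own figure.** The article gives no SD, alpha or sidedness, so the 80% cannot be reproduced independently. Solving backwards at two-sided 0.05: SD = 12 / [(1.960 + 0.842) × √(2/50)] = 12 / (2.802 × 0.2) = 21.4 pg/mL. This back-calculated SD is used below only to give scale.

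**Step 1: what each analysis contains.** In arm j (I = intervention, U = usual care), let p_j be the fraction without a 1-year BNP, C_j the completers' mean change and M_j the unobserved mean change in dropouts. The mean over everyone randomized is C_j + p_j(M_j − C_j). All contrasts are intervention minus usual care, so benefit is negative.

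Bias of the completers' contrast = p_U(M_U − C_U) − p_I(M_I − C_I).

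**Step 2: the ITT minus per-protocol difference, with the per-protocol set taken as completers.**

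| How the analyses are run | ITT minus per protocol | Does M_j enter? |
|---|---|---|
| ITT on observed cases | (C_I − C_U) − (C_I − C_U) = 0 | No |
| ITT with imputed dropout means m_j | p_I(m_I − C_I) − p_U(m_U − C_U) | No, only the imputed m_j |
| ITT on observed cases; per protocol also removes non-adherers | Effect of removing people whose BNP was observed | No |

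The bias in Step 1 depends on M_j, and M_j appears in none of the three rows. The planned comparison therefore cannot estimate the bias.

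**Step 3: illustration with unequal dropout.** The rates and the gap are assumptions. Take M_j − C_j = 20 pg/mL in both arms.

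- 10% intervention, 20% usual care: 0.20 × 20 − 0.10 × 20 = +2 pg/mL, which is 2/12 = 17% of the detectable difference. The standard error is 21.4 × √(1/45 + 1/40) = 4.65, so this is about 0.4 standard errors.
- 10% intervention, 30% usual care: 0.30 × 20 − 0.10 × 20 = +4 pg/mL, or 33%. The standard error is 21.4 × √(1/45 + 1/35) = 4.8, so this is about 0.8 standard errors.

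The positive sign means bias toward the null. With the excess dropout in the intervention arm the signs reverse.

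**Step 4: illustration with equal dropout rates.** 20,000 simulated trials per scenario; true effect 0, SD 21.4, 50 per arm. Dropout is random in usual care and, in the intervention arm, correlated 0.5 with a worse BNP change.

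| Dropout in each arm | Completers' bias (pg/mL) | False-positive rate | Bias if missing changes are set to zero (pg/mL) |
|---|---|---|---|
| 10% | −2.0 | 7% | −1.8 |
| 20% | −3.6 | 13% | −2.9 |
| 30% | −5.3 | 19% | −3.7 |

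On observed cases, ITT and completer results are identical in every row. With the simple zero-change imputation at 20% dropout they differ by 3.6 − 2.9 = 0.7 pg/mL. That would pass for agreement, although the true effect is 0 and both estimates are wrong by about 3 pg/mL or more. With dropout unrelated to BNP, bias is about 0 and the false-positive rate about 5%; on observed cases the ITT and completer results are again identical. The check does not separate the harmless case from the harmful one.

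**The case against.** A reader might go further and infer that the ITT statement is itself untrue, because someone without a 1-year BNP cannot enter a t-test. The document does not support that. Everyone randomized can be included if missing 1-year values are imputed or modelled under a stated assumption. How that is done is commonly left to a full protocol or SAP, and none is shown here. Its absence is not a finding. For the same reason, a zero difference between the two analyses follows only if ITT is run on observed cases.

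Other points on the plan's side:

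- The per-protocol set is undefined. It might exclude people who have a 1-year BNP but missed another part of the protocol. The two analyses would then differ, but only through people whose BNP was observed. Those with none would remain unexamined.
- Retention is reported by arm, so unequal dropout would be visible. That helps, but it shows how many left and not whether their BNP differed.
- Deaths, hospitalizations and ER visits are found by chart review and can be available after dropout. The point is confined to BNP and the other 1-year visit measures.
- The 20 pg/mL gap has no source and exceeds the 12 pg/mL detectable difference. The resulting biases are below one standard error. This is fair, and the figures serve only as illustration.
- This is a 100-person pilot without a formal power analysis, and the sentence concerns a secondary analysis.

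These arguments limit the scope and severity. None of them gives the per-protocol analysis information on those who dropped out.

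**Conclusion.** The point holds for the purpose assigned to the per-protocol analysis. It rests on two facts in the article: BNP is measured at baseline and 1 year with no interim value described, and the per-protocol analysis is named as the way to judge the influence of dropout. Whichever way ITT handles missing values, agreement between the two analyses would not show that dropout was harmless. A fuller SAP could add missing-data methods but would not make the sentence correct.

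The size of any bias is unknown. Under the assumed rates and gap, unequal dropout gives about 2 to 4 pg/mL, toward the null if the excess is in usual care. Dropout related to BNP in the intervention arm alone could instead favour the intervention. If dropout is unrelated to BNP there is no bias. Severity is moderate.

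**What to change.** 1. Remove the assessment of dropout as the purpose of the per-protocol analysis. Keep it as an adherence analysis, with the per-protocol set defined before the data are examined.
2. Assess dropout with a delta-adjusted (tipping-point) sensitivity analysis of missing 1-year BNP in all randomized participants. Impute the missing values, shift them by a prespecified range of deltas set separately in each arm, and report the delta at which the conclusion changes. This varies the quantity M_j − C_j directly, which the planned comparison never touches.
3. Alongside retention by arm, tabulate baseline values of dropouts and completers in each arm. This should be descriptive, since the numbers will be small.

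Electronic health record measurements near 1 year could serve as auxiliary variables in the imputation. This is optional, because the article does not establish that they exist for dropouts or may be used after withdrawal.

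The cost is a change of wording and modest programming, with no added visits or measurements. The downside is one extra sensitivity table that rests on assumptions.
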